## **7.2 Recruitment rates (See Figure 2: Projected participant recruitment and centre start up graph)**

### **7.2.1 Original Recruitment rates**

Across approximately 17 NHS centres, each serving populations of around 0.75 million, we aim to recruit an average of 3-4 per month per centre to achieve the target of 1000 participants over a 29 month recruitment period. The graph in Figure 2 illustrates the original projected participant recruitment and centre start up.

### **7.2.2 Updated Recruitment rates**

Recruitment has been ongoing for 36 months and will continue for another 12 months. We aim to recruit a new target of 1 participant per month per centre across approximately 22 NHS centres to achieve the revised target of 750 participants. The graph in Figure 3 illustrates the revised projected participant recruitment.

## **Figure 2: Projected participant recruitment and centre start up graph**

[figure not shown]

**Figure 3: Revised projected participant recruitment**

[figure not shown]

### 7.3 Milestones

The project timetable and milestones can be found in Appendix 1.

### 7.4 Feasibility phase

The internal feasibility phase will assess the key trial delivery parameters. The feasibility phase will

- Determine whether the proposed rate of recruitment is feasible;

- Monitor whether the allocated interventions are delivered within 8 weeks of randomisation;
- Finalise the optimum mode and timing of acute pain measurements.

The feasibility phase will be run as per any large multi-centre randomised trial. The feasibility phase will conclude with at least 23 centre months aggregated across at least three sites (with the expectation of at least 60 participants). This will present one of three situations:

1. Recruitment is within 75% of the target, in which case there is sufficient reassurance to continue unchanged to the main study
2. Recruitment is between 50% and 75% of the target rate, in which case the feasibility phase will continue with appropriate modifications (such as recruiting more centres, or allowing for more recruitment time at a centre)
3. Recruitment is less than 50% of the anticipated rate, in which case the study may not be feasible.

## **8. STATISTICAL ANALYSIS**

Treatment groups will be described at baseline and follow-up using means (with standard deviations), medians (with inter-quartile ranges) and numbers (with percentages) where relevant. Primary and secondary outcomes will be compared using generalised linear models, with adjustment for participant baseline and design covariates, (stone  $\leq 10$  mm and stone  $>10$ mm; location in ureter: upper, mid, or lower; age; and gender).

Statistical analysis will be per protocol and intention-to-treat (as is recommended for non-inferiority trials) with results displayed as estimates and 95% confidence intervals (CIs) derived from appropriate generalised linear models. CIs around observed differences will then be compared to the pre-specified non-inferiority margin. Subgroup analyses (appropriately analysed by testing treatment by subgroup interaction) will explore the possible effect modification by type and location of stone and gender; all using stricter levels of statistical significance ( $p < 0.01$ , 99% confidence intervals).

All analyses will follow a carefully documented Statistical Analysis Plan (SAP). The SAP will be available to both the Trial Steering Committee (TSC) and the independent Data Monitoring Committee (DMC) members should they wish to review and comment on the document. A single main analysis will be performed at the end of the trial when all follow up has been completed.

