## **3.3 Recruitment and Study Procedures**

### **3.3.1 Identifying participants**

Local procedures at the participating hospitals are different and the timing and mode of approach to patients and the consent process will vary to accommodate both the variability at the sites and the needs of the patients. Following adequate pain relief and confirmation of ureteric calculi by CTKUB, eligible patients (according to the inclusion and exclusion criteria given in sections 3.2.2) will be provided with a patient information leaflet (PIL).

Each patient will have the opportunity to discuss the study with the local clinical team. Patients may make a decision to participate, during a consultation with the local clinical team during a visit to hospital (e.g. when they attend a clinic appointment or whilst a patient in hospital for their initial stone episode) or alternatively at home. If the patient agrees to be contacted at home he/she may receive a telephone call from the local Research Nurse to discuss any queries. Patients who decide to participate following telephone counselling can either send their completed documents (consent form and baseline questionnaire) through the post to the local team at their treating hospital or bring it with them if they are returning to hospital for another consultation or treatment. Participants will be

randomised to one of the two treatment groups following consent, completion and receipt of baseline questionnaire.

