### **3.3.4 Follow-up procedures**

Eligible patients that have given signed informed consent to participate in the study will be asked to complete the EQ-5D, SF-12, pain score (NRS), use of analgesics at baseline and will then be randomised to either ESWL or ureteroscopic retrieval. Participants will be asked to complete the pain score, EQ5D, and use of analgesics questions (self completed) at their allocated intervention visit to secondary care immediately prior to receiving their interventions. At one week post intervention they will be asked to complete the pain score and use of analgesics questions by self completed questionnaire. Participants allocated to ESWL (up to two sessions of ESWL) will receive these questionnaires for their first session of ESWL. At eight weeks and then six months post randomisation participants will be asked to complete a questionnaire to measure the EQ-5D, SF-12, pain score (NRS), use of analgesics, complications, additional interventions received, and acceptability of the received procedure. In addition, at six months post randomisation, participants will be asked to complete questions relating to their primary and secondary care. Questionnaires and up to two reminders will be sent to participants by post, email or phone, taking into account any preferences they may have for mode of communication.. The case report forms (CRFs) at eight weeks and six months post randomisation will be completed and entered at site by the centre coordinators at the recruiting centres. They will collect additional interventions received and reasons for those, reasons why they might not have received their allocated intervention, complications and date of stone passage.

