### 5.2 Secondary outcome measures

**Patient-reported** -measured at pre and 1 week post intervention, 8 weeks and 6 months post randomisation

Severity of pain as measured by the Numeric Rating scale (NRS), generic health profile as measured by the SF-12, (8 weeks and 6 months only), health status as measured by the EQ5D, use of analgesia, acceptability of received procedure (8 weeks and 6 months only)

**Clinical** Further interventions received, complications up to 6 months post randomisation

**Economic** NHS primary and secondary care use and costs up to 6 months, patient costs; incremental cost per surgical interventions averted.

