### **9.4 Cost effectiveness**

The cost effectiveness will be measured in terms of costs of the treatment care pathways and quality adjusted life years (QALYs) at six months. QALYs will be estimated by transforming the EQ5D scores (collected at baseline, eight weeks and six months post-randomisation) into utility values using standard algorithms. The results will be presented as point estimates of mean costs, QALYs, and incremental cost per QALY of each treatment care pathway. Measures of variance for these outcomes are likely to involve bootstrapping estimates of costs and incremental QALYs. Incremental cost-effectiveness data will be presented in terms of cost-effectiveness acceptability curves (CEACs). Forms of uncertainty, e.g. concerning the unit cost of resources from the different centres, will be addressed using standard deterministic sensitivity analysis. Sensitivity analysis will also be used to explore the impact of statistical imprecision and other forms of uncertainty. Where feasible the results of the sensitivity analyses will also be presented as CEACs.

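### Section 8 lists the adjustment covariates without any baseline score, and section 9.4 mentions no adjustment for baseline utility, so some precision on patient-reported outcomes and QALYs is given away (minor)

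*Protocol*

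**What the plan says.** Section 8 (Statistical Analysis) makes one modelling statement for every outcome: "Primary and secondary outcomes will be compared using generalised linear models, with adjustment for participant baseline and design covariates". The bracket that follows spells the covariates out as stone size (two categories) and then "location in ureter: upper, mid, or lower; age; and gender". No baseline questionnaire score appears. The section closes by referring all analyses to a SAP, which is not at hand.

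The baseline scores exist. Section 3.3.4 says participants "complete the EQ-5D, SF-12, pain score (NRS), use of analgesics at baseline and will then be randomised", and section 3.3.1 places randomisation "following consent, completion and receipt of baseline questionnaire". Section 5.2 makes the same instruments secondary outcomes: pain NRS, analgesic use, and "generic health profile as measured by the SF-12, (8 weeks and 6 months only), health status as measured by the EQ5D".

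For the economic outcome, section 9.4 builds QALYs from EQ-5D at baseline, eight weeks and six months, and says: "The results will be presented as point estimates of mean costs, QALYs, and incremental cost per QALY of each treatment care pathway". Bootstrapping is the likely route to measures of variance. No covariates are given and adjustment for baseline utility is not mentioned.

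**The concern.** For a repeatedly measured continuous outcome, the participant's own baseline value is often the best single predictor of follow-up. Leaving it out widens the interval and lets a chance difference between arms at baseline pass partly into the treatment estimate. Here the value should be near complete, because the baseline questionnaire must be received before randomisation.

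The case is clearest for QALYs. Incremental cost per QALY is the primary economic outcome (section 5.1), and baseline utility enters the QALY directly. A chance imbalance in baseline EQ-5D therefore moves the QALY difference even if baseline does not predict follow-up. Bootstrapping describes the uncertainty but does not remove the imbalance.

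Section 3.3.4 also has a second pre-treatment measurement, taken after randomisation and just before the intervention, which section 5.2 counts as an outcome time point. Any later baseline adjustment should say which of the two it means.

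**Working it through.** **Inputs from the protocol.** Secondary-outcome power above 90% for 0.25 SD in the original design of 1000, or 450 per arm after 10% drop-out (section 7.1); revised total of 750, or 375 per arm (section 7.1); EQ-5D for QALYs at 0, 8 weeks and 6 months (section 9.4).

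**Assumed, because the documents do not give them.** Baseline-to-follow-up correlation r, range 0.2 to 0.5; 20% questionnaire non-response as a sensitivity case; linear area under the curve for QALYs.

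**1. The stated figure.** Power = Φ(0.25/√(2/n) − 1.96). At n = 450 per arm: 0.25/0.0667 = 3.75, and Φ(1.79) = 96.3%. The claim of above 90% is reproduced.

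**2. Same formula at the revised size.** At 375 per arm, 92.8%. With 10% drop-out (337.5 per arm), 90.1%. With an assumed 20% non-response (300 per arm), 86.5%.

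**3. Adding the baseline score.** Residual variance is multiplied by 1 − r², so power = Φ(0.25/√(2(1 − r²)/n) − 1.96). The equivalent total is 750/(1 − r²).

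| r | 1 − r² | Equivalent total | Power, 375/arm | Power, 337.5/arm | Power, 300/arm |
|---|---|---|---|---|---|
| not adjusted | 1.00 | 750 | 92.8% | 90.1% | 86.5% |
| 0.2 | 0.96 | 781 | 93.8% | 91.2% | 87.8% |
| 0.3 | 0.91 | 824 | 94.8% | 92.6% | 89.4% |
| 0.5 | 0.75 | 1000 | 97.7% | 96.3% | 94.2% |

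The first row has no covariates at all. Section 8 already adjusts for four. So far as these share information with the baseline score, the gain over the section 8 model is somewhat smaller than the table shows.

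**4. Chance imbalance.** The standard error of the baseline difference at 375 per arm is √(2/375) = 0.073 SD. An imbalance of 1.96 standard errors is 0.143 SD. Without the baseline score it moves the estimate by about r × 0.143:
- r = 0.2: 0.029 SD, 11% of 0.25 SD
- r = 0.3: 0.043 SD, 17%
- r = 0.5: 0.072 SD, 29%

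**5. QALY weights.** With straight lines between 0, 8 and 26 weeks, the weights in years are:
- baseline: (8/2)/52 = 0.077
- eight weeks: (26/2)/52 = 0.250
- six months: (18/2)/52 = 0.173

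They sum to 0.5. Baseline holds 4/26, about 15%. That share of an imbalance enters directly; anything further depends on r.

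**The case against.** The strongest reply is that this is SAP detail. Section 8 defers to a SAP, and outcome-specific covariates are commonly set there. The bracket serves all outcomes at once, including a binary primary outcome with no baseline value, so it would naturally hold only shared covariates. It may also not be a closed list: centre is a minimisation factor in section 3.3.3 and is missing from it. In an acute, resolving condition r may be low, and at r = 0.2 the gain is about one power point at 375 per arm.

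Much of this stands, and it limits the severity. It does not remove the point. The protocol does not leave the covariates open; it itemises them without marking them as examples. A SAP that followed the text literally would omit the baseline scores.

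A reader might infer more than the documents support:
- *That the secondary outcomes are compared unadjusted.* They are not; section 8 adjusts for four covariates.
- *That section 9.4 excludes baseline utility.* It has no covariate list. It is silent, which is weaker.
- *That the treatment estimates are biased.* They are unbiased over repeated randomisation; the issue is precision and the imbalance that happens to occur.

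**Conclusion.** The point holds as a free improvement of minor severity. Section 8 names no baseline score although four suitable measures are collected before randomisation, and section 9.4 does not mention adjustment for baseline utility.

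For r between 0.2 and 0.5 the variance would fall by about 4% to 25% against a model without covariates, and somewhat less against the section 8 model. The range is assumed and could be wrong for acute pain in particular. The 15% QALY weight rests on a linear area under the curve, a method the protocol does not name.

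It would be tempting to say that the secondary-outcome power claim fails. It does not. The claim was made for the original size, where it is reproduced at 96.3%, and without the baseline score power is still 90.1% at 750 with 10% drop-out. It falls below 90% only under the assumed 20% non-response. The primary clinical outcome is not affected.

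**What to change.** Two additions:

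- **Section 8:** each patient-reported outcome with a pre-randomisation measurement (pain NRS, SF-12, EQ-5D, analgesic use) is also adjusted for its own value on the recruitment questionnaire, not for the pre-intervention value taken after randomisation. Acceptability of the procedure is excepted, because it has no baseline.
- **Section 9.4:** incremental QALYs are estimated by regression on arm, baseline EQ-5D utility and the section 8 covariates, with this regression repeated within the bootstrap.

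The cost is wording only, since the data are already collected. Fixing the covariates before the final analysis also prevents a choice made after seeing the results. If the SAP already contains these adjustments, it is enough to bring the protocol text into line with it.

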### STUDY ENTRY

Consent to the RCT will be obtained from 750 eligible patients after written and oral information is provided by local hospital teams. Eligible and consenting participants will be randomised to one of the two intervention groups. Randomisation will be stratified by centre, stone size ( $\leq 10$ mm or  $> 10$ mm, as measured by the maximum stone diameter on CTKUB) and location of the stone in either the upper, mid or lower ureter (as defined in the European Association of Urology-American Urological Association (EAU-AUA) Guidelines). Participants will be followed-up by postal questionnaires sent from the trial office (CHaRT, Aberdeen) at eight weeks and six months after randomisation and from their health record.

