### **3.3.3 Randomisation and allocation**

Eligible and consenting participants will be randomised to one of the two intervention groups using the telephone Interactive Voice Response (IVR) randomisation application or via the web based application - both hosted by the fully registered with the UK Clinical Research Collaboration (UKCRC), Clinical Trials Unit (CTU) at the Centre for Healthcare Randomised Trials (CHaRT), Health Services Research Unit (HSRU) in Aberdeen.

Randomisation will be minimised by centre, stone size ( $\leq 10\text{mm}$  or  $> 10\text{mm}$ , as measured by the maximum stone diameter on CT KUB) and location of the stone in either the upper, mid or lower ureter (as defined in the EAU/AUA Guidelines).

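### Centre is used to balance allocation but is missing from the closed list of adjustment covariates in Section 8; separately, the subgroup factor stone 'type' is undefined

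*Protocol*

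**What the plan says.** **Allocation.** Section 3.3.3 states "Randomisation will be minimised by centre, stone size" (cut at 10 mm) and location in the upper, mid or lower ureter. The Study Entry paragraph of the Protocol Summary names the same three factors, though under a different label: "Randomisation will be stratified by centre, stone size".

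**Analysis model.** Section 8 compares primary and secondary outcomes by generalised linear models "with adjustment for participant baseline and design covariates". The brackets that follow give stone size in two classes and then "location in ureter: upper, mid, or lower; age; and gender". Nothing in the brackets marks the list as examples only.

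**Subgroups.** Interaction tests "will explore the possible effect modification by type and location of stone and gender", at p<0.01 with 99% intervals. The protocol does not say what the type of a stone is.

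**SAP.** Section 8 refers all analyses to a separate statistical analysis plan, which is not available here.

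**The concern.** Section 8 sets out to adjust for the design factors and then names only two of the three. Had it said design covariates and stopped, the SAP could have supplied them. Because it enumerates them, a SAP that follows the list leaves centre out, and a SAP that includes centre departs from the protocol.

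The protocol itself gives reasons to expect centres to differ. Section 2 says the primary outcome turns on a decision by an unblinded treating clinician. Section 3.1 describes a variety of lithotripsy systems with only some standardisation. Section 3.3.1 says that local procedures differ. If success rates vary by centre and allocation is balanced within centre, the arm difference is estimated more precisely than a model without centre reports. At stake is a little precision on the bound that is compared with -0.20.

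The subgroup wording is a separate matter and has no bearing on that interval. An undefined factor can be given a meaning after the data are seen. Stone size, by contrast, is recorded for every participant at randomisation, and Section 1.2 cites it as one of the two factors by which the guideline evidence was stratified.

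**Working it through.** **Inputs from the protocol (Sections 7.1 and 7.2.2).** Success 0.75 with ureteroscopy and 0.65 with ESWL; margin 0.20; two-sided 95% interval; 750 participants, taken as 375 per arm; stated power 85%; about 22 centres.

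**Step 1. Reproduce the stated power.**
- Variance sum: 0.75 × 0.25 + 0.65 × 0.35 = 0.1875 + 0.2275 = 0.415.
- Standard error: √(0.415/375) = 0.0333.
- Distance from the expected difference to the margin: 0.20 − 0.10 = 0.10.
- Power: Φ(0.10/0.0333 − 1.96) = Φ(3.006 − 1.96) = Φ(1.046) = 85.2%, against 85% stated.

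The same formula gives 79.2% at 319 per arm (638 in total), against about 80% stated. For 90% power it needs 437 per arm, against the 450 that the protocol obtained by simulation. The plan's figures stand, and none of them depends on whether centre is in the model.

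**Step 2. Add centre.** The protocol gives no between-centre variance, so the between-centre SD in success, s, is an assumption. With exact balance within centre and a centre effect common to both arms, adjustment removes s² from each arm's variance:

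residual variance sum = 0.415 − 2s²; power = Φ(0.10/√(residual/375) − 1.96).

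| Assumed s | Residual sum | Standard error | Power with centre |
|---|---|---|---|
| 0 | 0.415 | 0.0333 | 85.2% |
| 5 points | 0.410 | 0.0331 | 85.6% |
| 10 points | 0.395 | 0.0325 | 86.9% |
| 15 points | 0.370 | 0.0314 | 88.9% |

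The width ratio without centre to with centre is √(0.415/residual): 1.006 at 5 points and 1.025 at 10 points. The half-width of the 95% interval is 1.96 × 0.0333 = 6.5 points without centre. With centre it is 6.5 and 6.4 points respectively.

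**Step 3. Direction of the error.** The same question can be put in terms of an assumed intraclass correlation (ICC), with the outcome variance scaled by 1 − ICC. If centre is balanced but omitted, the true one-sided error is Φ(−1.96/√(1 − ICC)), against a nominal 0.025.

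| Assumed ICC | One-sided error, centre omitted | Power, centre omitted | Power, centre included |
|---|---|---|---|
| 0.02 | 0.0239 | 85.5% | 85.9% |
| 0.05 | 0.0222 | 85.8% | 87.0% |
| 0.10 | 0.0194 | 86.5% | 88.7% |

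An SD of 5, 10 or 15 points corresponds to an ICC of s²/0.2075, which is about 0.01, 0.05 and 0.11. Power with centre omitted is itself a little above 85.2%, because balance already reduces the true variance. The like-for-like gain is therefore smaller than the gap from 85.2%: at an ICC of 0.05 it is 87.0 − 85.8 = 1.2 points.

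**Step 4. Simulation check.** Trials of 750 participants in 22 centres, with allocation balanced within centre, gave power without and with centre of 85.8% and 86.2% (ICC 0.02), 85.9% and 86.9% (0.05), and 86.1% and 87.5% (0.10). Simulated error without centre was 0.023 and 0.021 at the first two values, as the formula predicts. At 0.10 it was 0.024 without centre and 0.029 with it, which does not match the formula. That run used truncated centre effects and a fixed-effect model, and the Monte Carlo standard error is about √(0.025 × 0.975/10,000) = 0.0016. No weight is placed on that last result in either direction.

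**The case against.** - **Effect small and in the safe direction.** This stands. Omitting centre lowers the true one-sided error and costs at most a point or two of power over the range considered. The 15-point row would put centre success rates roughly 30 points either side of the mean, and nothing in the protocol supports that.
- **The gain is an upper bound.** This stands. Minimisation over three factors balances centre only approximately. Lithotripter differences would act mainly in the ESWL arm, and an added centre intercept does not recover treatment-by-centre variation.
- **Centre adjustment can be awkward.** This stands in part. With about 22 centres, some possibly small, and a binary outcome, fixed centre terms may be sparse. That bears on how centre enters the model, not on whether it is listed.
- **The SAP may deal with it.** How centre is modelled is properly left to the SAP. The closed list, however, is in the protocol and conflicts with its own description of design covariates.

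Two stronger readings are tempting. A reader might infer that Section 8 fails to analyse by the allocation factors at all. It does not: size and location are both in the model, and only centre is missing. A reader might also infer that the subgroup by 'type' cannot be run, or that 'type' must mean size. The contents of the baseline form are not shown, so whether a stone type is recorded is unknown. Table 1 lists outcome measures, and stone size and location are not in it either. Subgroups need not mirror the allocation factors, and the text does not settle the intended meaning.

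**Conclusion.** The inconsistency is real and its consequence is minor. Centre is an allocation factor in both places where allocation is described, and it is absent from the list that Section 8 presents as covering the design covariates. The interval compared with -0.20 is then about 0.6% to 2.5% wider than it need be, if the between-centre SD is 5 to 10 points, allocation is balanced within centre, and the centre effect is the same in both arms. Power at 375 per arm would rise from 85.2% to at most about 85.6% to 86.9%. With no centre variation nothing changes. The protocol's 750 participants and 85% power stand, and the omission does not make a false finding of non-inferiority more likely.

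The undefined subgroup factor is a separate and smaller wording defect.

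**What to change.** 1. Add centre to the covariate list in Section 8. A random intercept is a reasonable choice given about 22 centres, some of them possibly small; the detail can go in the SAP.
2. State that the adjusted primary result is reported as a risk difference with its 95% interval, so that it can be set directly against -0.20.
3. In the subgroup sentence, replace 'type' with stone size (≤10 mm / >10 mm) if that was meant. Otherwise define the term and state how it is recorded.

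The cost is wording only. Centre and stone size are already held in the randomisation record, and no extra participants are needed. The change should be made before the unblinded comparative analysis.
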